| 
1. Compare the impact of the online vestibular rehabilitation tool with standard written instructions after acute onset vertigo on different aspects of everyday living (superiority).
 
2. Compare how the online vestibular rehabilitation tool influences the walking ability and standing balance compared with standard written instructions after acute onset vertigo (superiority).
 
3. Compare how the online vestibular rehabilitation tool influences the lateral canal vestibulo-ocular reflex (VOR) recovery compared with standard written instructions after acute onset vertigo (superiority).
 
4. Compare the long-term effects of early vs. delayed online vestibular rehabilitation on vestibular symptoms and mobility (superiority).
 
5. Compare the effects of online vestibular rehabilitation with standard written instructions on vestibular rehabilitation compliance (superiority).
 
6. Compare the health economic effects of online vestibular rehabilitation with standard written instructions (superiority).
 
7. Compare the kinematic output data from a portable multi-sensor movement analysis system, with the kinematic output data received from the mobile phone app (comparative and partly superiority).
 | 
1. The between groups mean dizziness handicap inventory (DHI) score at 6 weeks and 3 months after vertigo onset.
 
2. The between groups changes in timed 25-foot walk test (T25-FW) from baseline to 6 weeks and 3 months; the between groups body sway during standing and walking; and the mobility at 6 weeks and 3 months after vertigo onset.
 
3. The between groups changes in video head impulse test (vHIT, site-dependent) measured lateral canal VOR gain and saccades from baseline at 6 weeks and 3 months after vertigo onset.
 
4. The between groups mean vertigo symptom scale short form (VSS-SF) score at 12 months after vertigo onset; and the between group pedometer-derived number of steps walked since last visit at 6 weeks and 3 months after vertigo onset.
 
5. The between groups mean number of weekly training sessions at 6 weeks.
 
6. Health economic effects on all levels of care (primary, specialized) and society (sick leave).
 
7. The added-value from using a multi-sensor movement analysis system to receive multi-joint kinematic output, in comparison to using a mobile phone placed on the hip to receive center-of-mass kinematic output.
 |

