| 9. Investigate the frequency of benign positional paroxysmal vertigo (BPPV) after AVS at different time point and using different evaluation methods; investigate the correlation between BPPV and the DHI, VSS-SF, steps and safety endpoints; and investigate the effect of treatment arm allocation on the risk for BPPV. | 9. The frequency (percentage) of participants with:
BPPV at 3 months after AVS onset; symptoms indicating BPPV 6 weeks after an AVS using a BPPV specific questionnaire;
positional nystagmus (non-BPPV) 3 months after an AVS; positional vertigo (non-BPPV) 3 months after an AVS;
BPPV in the treatment vs control group; and the DHI/VSS-SF/steps/safety results differences between the BPPV, suspected BPPV and non-BPPV groups. |
| Safety objective                                                                                                                                                                                                                                                                                                      | Safety endpoint                                                                                                                                                                                                                                                                                                                                                                                                                          |
| Compare the effects on the risk of falls and fractures and any other of online vestibular rehabilitation compared with standard written instructions.                                                                                                                                                                        | The proportion of participants who has experienced falls/fractures since study start up until 6 weeks, 3 months and 12 months; and the number of falls/fractures in each study arm at the same time points.                                                                                                                                                                                                                                     |

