## 6. Design of the clinical investigation

### 6.1. General information

This is a two-armed evaluator-blinded multicenter randomized controlled clinical trial investigating the effects of online vestibular rehabilitation compared with standard written instructions after acute onset vertigo. The standard care study arm will be granted access to the online rehabilitation tool at 3 months after enrollment.

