weekly online sessions consist of educational texts, symptom control techniques, scoring tests and exercise prescriptions for the following week. The exercises for the following week after each online session will be adapted to the user and thus become successively more difficult if the user scores lower discomfort during evaluations, or the opposite if the user scores higher discomfort. There are 6 different exercises in the tool: 1. Head shake with open eyes, gaze following the head; 2. Head nod with open eyes, gaze following the head; 3. Head shake with closed eyes; 4. Head nod with closed eyes; 5. Head shake with open eyes, gaze fixated and; 6. Head nod with open eyes, gaze fixated. These exercises are performed sitting, standing and walking depending on symptom intensity. There are 4 symptom control techniques in the tool in order to deal with secondary anxiety issues related to the vertigo: 1. Controlled breathing; 2. Relaxation; 3. Stress management and; 4. Thought control.

Control: After randomization written instructions with the 6 different exercises from the online rehabilitation tool is handed out and the participant is instructed to increase difficulty if possible. Participants are also given general advice to prevent inactivity and secondary dizziness and fear of motion. Data collection as for the intervention arm. At the end of the core study at 3 months from randomization the standard care study arm participants will also be granted access to the online rehabilitation tool and followed until 12 months.

The Swedish translations of VSS-SF, DHI, and EQ-5D-3L are collected locally at all sites by the site study coordinator. These questionnaire data will be collected by in-person interview at day 0, week 6 and after 3 months, except for VSS-SF at 6 weeks (primary endpoint) which will be collected by phone call interview by a blinded study coordinator at either the same site or a different site. In the case of the first 100 included subjects, the VSS-SF at 6 weeks (primary endpoint) will be collected by phone call interview twice, 48 hours apart, as part of the statistical validation of the Swedish translation of the VSS-SF questionnaire. Also, at week 3 and after 12 months VSS-SF and EQ-5D data will be collected by phone call interview (figure 1).

The T25-FW data will be collected by letting the subject walk a clearly marked 25-foot course during follow-up appointments at each site.

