**Table 2. Aim-specific statistical analysis plan**

| Analysis                                                                        | Subjects analyzed                         | Sample size (15% attrition is expected in power calc.) | Estimated difference based on previous results mean (SD) | Power   | Method                     |
|---------------------------------------------------------------------------------|-------------------------------------------|--------------------------------------------------------|----------------------------------------------------------|---------|----------------------------|
| Between group mean VSS-SF difference @w3, @w6, @m3, @m12                        | All participants                          | 92+92                                                  | 8.1 (7.4) vs 11.5 (9.9)                     | 90%     | ANCOVA                     |
| Between group mean EQ-5D difference until m3                                    | All participants                          | 92+92                                                  | Unknown                                                  | Unknown | Mixed models               |
| Between group mean EQ-5D difference @12m                                        | All participants                          | 92+92                                                  | Unknown                                                  | Unknown | ANCOVA                     |
| Between group mean DHI difference until m3                                      | All participants                          | 92+92                                                  | 24.4 (20.8) vs 29.2 (21.1)                  | 68%     | Mixed models               |
| Mean of means T25-FW (seconds) and timed balance tests (seconds) until m3       | All participants                          | 92+92                                                  | Unknown                                                  | Unknown | Mixed models               |
| Between group mean difference of means of vHIT gain (affected side) @w6 and @m3 | Participants at sites with access to vHIT | 50+50                                                  | 0.52 (0.24) vs 0.69 (0.25) *31                | 99%     | Ranked ANCOVA              |

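### The 12-month falls and fractures readout is labelled tool versus written instructions, but controls are granted the tool at 3 months, so it compares early with delayed access

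*Protocol*

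**What the plan says.** **Control access.** Section 6.1 of the protocol states: "The standard care study arm will be granted access to the online rehabilitation tool at 3 months after enrollment". Section 6.7 repeats it: "At the end of the core study at 3 months from randomization the standard care study arm participants will also be granted access". It adds that these participants are then followed to 12 months.

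**Safety.** Section 5.2 gives the objective as "Compare the effects on the risk of falls and fractures and any other of online vestibular rehabilitation compared with standard written instructions". The endpoint beside it is "The proportion of participants who has experienced falls/fractures since study start up until 6 weeks, 3 months and 12 months", together with the number of such events per arm at the same times. The falls and fractures row of Table 2 names a logistic regression but no time point.

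**Health economics.** Objective 6 reads "Compare the health economic effects of online vestibular rehabilitation with standard written instructions (superiority". Its endpoint covers care use and sick leave, with no time horizon. Section 6.3 makes EQ-5D the source of the QALYs. Table 2 has one EQ-5D row running to 3 months (mixed models) and a second, "Between group mean EQ-5D difference @12m" (ANCOVA).

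**Where delayed access is acknowledged.** Objective 4 in section 5.2 calls the long-term contrast early versus delayed rehabilitation, but only for vestibular symptoms and mobility. Section 6.7 describes the 12-month telephone contact as a way to pick up lasting effects of intervening early.

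**The concern.** A comparison with written instructions needs a control arm that has only written instructions. From 3 months that is no longer the planned control condition. Randomization still makes the 12-month comparison a fair one, but the question it answers is whether getting the tool at the start differs from getting it three months later. The safety objective attaches the other label to it.

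The label governs what may be concluded. If the tool affects falls whenever it is used, late use by controls brings the arms closer together. A benefit can then look smaller than it is, and so can an excess of falls, which is the less cautious direction for a safety result. Section 8.2.1 also takes falls and fractures out of adverse event reporting because they are endpoints in their own right, so this endpoint is the main between-arm view of them. Section 3.3 calls the trial pivotal and confirmatory.

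**Working it through.** The protocol gives no event rate, cost or power for the falls, EQ-5D or cost comparisons, so there is no figure of its own to reproduce. The check rests on timing, with an illustration added.

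**1. Share of the 12-month window after control access.** Inputs from Table 1: 3-month target day 90 ± 7; 12-month target day 360 ± 14. Control access is taken to coincide with the 3-month visit.

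Share = (day of 12-month contact − day of access) / day of 12-month contact

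- Target days: (360 − 90)/360 = 270/360 = 75%
- Lowest: (346 − 97)/346 = 249/346 = 72%
- Highest: (374 − 83)/374 = 291/374 = 78%

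**2. Each readout against its label.**

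| Readout | Control access before it? | What it compares |
|---|---|---|
| Falls/fractures to 6 weeks | No | Tool versus written instructions |
| Falls/fractures to 3 months | No, apart from the visit window | Tool versus written instructions |
| Falls/fractures to 12 months | Yes, 270 of 360 days | Early versus delayed access |
| EQ-5D to 3 months | No, apart from the visit window | Tool versus written instructions |
| EQ-5D at 12 months | Yes, for the preceding 270 days | Early versus delayed access |
| Objective 6 costs and QALYs | Depends on the horizon, which is not stated | Early versus delayed access if past 3 months |

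The visit window matters little. If access were opened on day 90 and the visit took place on day 97, 7 of 97 days would be affected (7%).

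**3. Illustration of dilution.** Assumptions, none of them from the documents: a constant underlying fall rate over 12 months; a rate ratio r that applies throughout the time the tool is available; and a fraction u of controls taking the tool up at 3 months.

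Observed 12-month ratio = 12r / (3 + 9 × [1 + u(r − 1)])

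- r = 0.70, u = 1: 8.4/(3 + 6.3) = 8.4/9.3 = 0.90
- r = 0.70, u = 0.5: 8.4/(3 + 7.65) = 8.4/10.65 = 0.79
- r = 1.40, u = 1: 16.8/(3 + 12.6) = 16.8/15.6 = 1.08
- r = 1.40, u = 0.5: 16.8/(3 + 10.8) = 16.8/13.8 = 1.22
- u = 0: no dilution; the ratio stays at r

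These ratios concern the number of falls. The proportion with at least one fall would behave differently, depending on the underlying rate.

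**The case against.** The case on the other side is that this is an openly delayed-access design whose authors know what their 12-month data are. Section 6.7 ends the core study at 3 months and ties the 12-month contact to early intervention. Objective 4 uses the early-versus-delayed wording. Table 2 already splits EQ-5D at 3 months. Safety is also read at 6 weeks and 3 months, so an early excess of falls would not be hidden. All of this stands, and it narrows the point to the later readouts. It does not change the safety objective, which gives one label to all three time points.

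A reader might infer more than the documents support:

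- **That objective 6 compares the arms over 12 months.** It does not say so. Collecting EQ-5D for QALYs and comparing it at 12 months suggests such a reach, but no horizon is stated, and an economic horizon is often left to a later plan.
- **That 75% of the events are affected.** The figure is a share of calendar time. Section 3.2 cites persisting symptoms at 3 months in 30–50% of patients, so falls related to vertigo could be concentrated early.
- **That the effect lasts all year.** The programme runs for 6 weeks (section 2.1), so the constant effect in the illustration is only an assumption.
- **That controls use the tool after month 3.** They are granted access; their uptake is not given.
- **That early access contaminates the 3-month visit.** Section 6.7 ties access to the end of the core study, and Table 1 makes the 3-month visit the last at the site. The natural reading is access at or after that visit.

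**Conclusion.** The point holds for the 12-month falls and fractures readout. It is worded as tool versus written instructions, while 75% of its window (72% to 78%) follows control access, so it can only be read as early versus delayed access. The same reading applies to EQ-5D at 12 months and to any cost or QALY result that runs past 3 months. The size of any dilution is unknown: it runs from none, if no control takes up the tool, to 0.70 becoming 0.90 or 1.40 becoming 1.08 under full uptake and the assumptions above.

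The 6-week and 3-month safety readouts remain sound comparisons with written instructions. The 6-week primary endpoint and the pass criterion in section 9.5 are untouched. This is a correction to what one secondary result may be said to show, and it should be made before the results are read.

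A separate contradiction bears on the same readout: Table 1 marks falls and fractures at 6 weeks and 3 months but not at 12 months. Complete 12-month data would not cure the labelling problem.

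**What to change.** In section 5.2 and Table 2:

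- State that the comparison of falls and fractures between the tool and written instructions runs from randomization to 3 months, and add time points to the falls and fractures row of Table 2.
- Label the 12-month falls and fractures result and the 12-month EQ-5D result as early versus delayed access, in line with objective 4.
- Apply the same label to any cost, sick leave or QALY result under objective 6 that extends beyond 3 months, and state the horizon used.

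The cost is a few lines of wording, plus a 3-month cut-off date per participant in the register data if a direct economic contrast is wanted. No data are discarded, because the 12-month results are still reported under a label that fits them. The downside is that the direct safety contrast covers 90 of 360 days (25%) and will contain fewer events, so its confidence interval will be wider.

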|                                                 | 
6. Register-based search for health economic effects on all levels of care (primary, specialized) and society (sick leave).
 
7. The difference in kinematic output between measurement systems (i.e., multi-sensor and mobile app) during the tests specified in 2a and 2b.
 
8. The reliability and validity of the Swedish VSS-SF translation.
 
9. The frequency (percentage) of participants with:
BPPV at 3 months after AVS onset;
symptoms indicating BPPV 6 weeks after an AVS using a BPPV specific questionnaire;
positional nystagmus (non-BPPV) 3 months after an AVS;
positional vertigo (non-BPPV) 3 months after an AVS;
BPPV in the treatment vs control group; and
the DHI/VSS-SF/steps/safety results differences between the BPPV, suspected BPPV and non-BPPV groups.
 
Safety endpoint:
The proportion of participants who has experienced falls/fractures since study start up until 6 weeks, 3 months and 12 months; and the number of falls/fractures in each study arm at the same time points.
 |
| Planned duration of the clinical investigation: | October 2021 –December 2024                                                                                                                                                                                                                                                                                                                                                                                                                                                                                                                                                                                                                                                                                                                                                                                                                                                                                                                                                                                                                                                             |

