Basic body sway data will be collected by each site study coordinator using a locally developed application which utilizes cell phone built-in motion tracking. An enhanced gait analysis with a wearable motion tracking system will be performed at Umeå University Hospital for in-depth measurements.

The participants will be instructed to keep a provided pedometer on them as often as possible during the first 3 months. The total number of steps for the first 6 weeks, and from week 6 to 3 months will be recorded into REDCap will be compared between the study arms at week 6 and after 3 months.

At sites with access to vHIT we will also measure VOR gain and catch-up saccades by performing vHIT at day 0, 6 weeks and 3 months.

The catch-up saccades (yes/no, proportion of impulses with saccades) will also be compared between the study arms at 6 weeks and 3 months (affected side).

The 12 months data collection to capture potential long-term effects of early intervention will be performed by the Umeå University Hospital study coordinator by contacting all participants by telephone at 12 months after inclusion. During this phone call one last round of VSS-SF questionnaire data will be collected (Figure 1).

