**Table 1. Schedule of events**

| Visit/contact                       | Baseline | 3 weeks
(by phone) | 6 weeks | 3 months | 12 months (by
phone) | Comments                                            |
|-------------------------------------|----------|-----------------------|---------|----------|-------------------------|-----------------------------------------------------|
| Target day                          | 0        | 21 +/-3               | 42 +/-3 | 90 +/-7  | 360 +/-14               |                                                     |
| Eligibility
screening, history   | x        |                       |         |          |                         |                                                     |
| Randomization                       | x        |                       |         |          |                         |                                                     |
| VSS-SF                              | x        | x                     | x       | x        | x                       | Primary endpoint @6
weeks                        |
| EQ-5D                               | x        |                       | x       | x        | x                       |                                                     |
| DHI                                 | x        |                       | x       | x        |                         |                                                     |
| T25-FW                              | x        |                       | x       | x        |                         |                                                     |
| Body sway                           | x        |                       | x       | x        |                         |                                                     |
| Enhanced body
sway analyses      | x        |                       | x       | x        |                         | At selected sites only                              |
| vHIT                                | x        |                       | x       | x        |                         | At selected sites only                              |
| Steps, falls and
fractures       |          |                       | x       | x        |                         | Total steps, since
enrollment or last visit      |
| BPPV questions                      |          |                       | x       | x        |                         |                                                     |

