| BPPV testing                        |          |                       |         | x        |                         |                                                     |
| Compliance                          |          | x                     | x       |          |                         | Questionnaire data,
number of weekly
sessions |
| Trial termination
form (local)   |          |                       |         | x        |                         | Last site visit @ 3
months                       |
| Trial termination
form (central) |          |                       |         |          | x                       |                                                     |
| Estimated time
requirement       | 150 min  | 15 min                | 120 min | 120 min  | 15 min                  | Total 7 hours per
participant                    |

Abbreviations: VSS-SF = vertigo symptom scale short form; EQ-5D = EuroQol five-dimension scale; DHI = dizziness handicap inventory; T25-FW = timed 25-foot walk test; SD = standard deviation; vHIT = video head impulse test.

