## 8.2. Recording and Reporting

### 8.2.1. Recording

The PI or an authorized designee will record in the eCRF:

- all AEs except the events below specified not to be recorded:
  - Vertigo, nausea or mild discomfort during the vestibular rehabilitation, regardless of randomization allocation. These symptoms are common after acute vertigo and during vestibular rehabilitation and all subjects are expected to develop such symptoms.
  - Falls and fractures are recorded and reported as stand-alone endpoints and therefore not included in the AE reporting.
  - VSS-SF (Vertigo Symptom Scale - Short Form) measures the frequency of 15 known vestibular symptoms and these are recorded and reported as endpoints and therefore not included in the AE reporting.
- all SAEs
- all DDs
- any new finding in relation to any of the above-mentioned events.

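### The safety endpoint runs to 12 months, but no collection of falls and fractures is scheduled after 3 months

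*Protocol*

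**What the plan says.** Section 5.2 gives one safety endpoint in two parts. The first is "The proportion of participants who has experienced falls/fractures since study start up until 6 weeks, 3 months and 12 months". The second is "the number of falls/fractures in each study arm at the same time points". The synopsis states the same endpoint with the same three time points.

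Collection is described in three places:

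- **Schedule of events (Table 1).** The row "Steps, falls and fractures" is marked at 6 weeks and 3 months. Its 12-month cell is empty. The local trial termination form carries the comment "Last site visit @ 3 months".
- **Section 6.7.** On the telephone contacts it says that "at week 3 and after 12 months VSS-SF and EQ-5D data will be collected by phone call interview". Of the 12-month contact it says: "During this phone call one last round of VSS-SF questionnaire data will be collected". Falls and fractures are named in neither place.
- **Section 8.2.1.** Among the exceptions to adverse event recording it says: "Falls and fractures are recorded and reported as stand-alone endpoints and therefore not included in the AE reporting". All SAEs are listed as a separate item to be recorded.

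Table 2 plans a binary logistic regression for the proportion with falls or fractures in all participants (92+92), without naming a time point.

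**The concern.** The endpoint definition and the data collection do not match. The protocol promises a cumulative result at three time points and schedules collection for two. Normally, adverse event recording would fill such a gap. Here section 8.2.1 closes that route for non-serious events, on the ground that falls and fractures are recorded as endpoints. After 3 months no endpoint recording is scheduled, so the reason for the exclusion has gone while the exclusion still applies.

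At stake is one of the three time points of the only stated safety endpoint. A lower risk of falls is also one of the benefits expected in section 4.1. If the data to 3 months were reported as the cumulative 12-month figure, both the proportion and the count would be lower bounds. An analysis plan cannot repair this, because the data would not have been collected.

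**Working it through.** The protocol states no figure to reproduce here. The check sets the passages side by side and then measures the uncovered window.

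**Step 1. Required against scheduled**

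| Time point | Required (synopsis, 5.2) | Falls and fractures in Table 1 | Section 6.7 text |
|---|---|---|---|
| 6 weeks (day 42 ±3) | yes | marked | not needed to settle the point |
| 3 months (day 90 ±7) | yes | marked | not needed to settle the point |
| 12 months (day 360 ±14) | yes | empty | VSS-SF and EQ-5D only |

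In the same table VSS-SF and EQ-5D are marked at 12 months, so the 12-month column was read correctly and the empty cell is specific to this row.

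**Step 2. Other routes to the data after 3 months**

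- *Adverse event recording.* Closed for non-serious falls and fractures by section 8.2.1.
- *SAE recording.* All SAEs form a separate item in section 8.2.1, and section 8.1.3 counts hospitalization as an SAE criterion. A serious fall or fracture is probably still recorded, although the text does not say so.
- *Registers.* The synopsis specifies a "Register-based search for health economic effects on all levels of care (primary, specialized) and society (sick leave"). Its stated purpose is health economics. It could show fractures treated in care, but not untreated falls.

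Neither of the last two routes gives the proportion with any fall or fracture, or the number of them, as section 5.2 defines it.

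**Step 3. Length of the window without scheduled collection**

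Inputs: last scheduled collection at day 90 (window 83 to 97); end of the endpoint at day 360 (window 346 to 374), both from Table 1.

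Uncovered share = (end day − last collection day) / end day

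- Target days: (360 − 90) / 360 = 270 / 360 = 75%.
- Shortest: (346 − 97) / 346 = 249 / 346 = 72%.
- Longest: (374 − 83) / 374 = 291 / 374 = 78%.

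**Step 4. Can a prospective change complete the endpoint?**

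Section 9.6 reports 138 subjects included by 25 April 2023, and the synopsis gives a planned start in October 2021. Counting 360 days back from 25 April 2023 gives 30 April 2022. Participants enrolled up to about then had already reached the 12-month target day. The protocol does not give their number. A question added now gives no data for anyone whose call has already taken place.

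**The case against.** The best reply is that the loss is smaller than it looks, and much of that reply stands.

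- **The randomised comparison is covered where it is cleanest.** The safety objective compares the online tool with written instructions. Controls receive the tool at 3 months, so the arms differ in access only until then, and both time points in that period are scheduled. This stands: the 6-week and 3-month results are intact.
- **A reader might infer that an early-versus-delayed safety comparison is lost.** The documents do not support this. Early versus delayed access is secondary objective 4, and it concerns vestibular symptoms and mobility, not safety.
- **A reader might infer that nothing about falls or fractures is captured after 3 months, or that 75% of events are lost.** Neither follows. SAEs are listed separately from the excluded adverse events. The 75% is calendar time, and the protocol gives no fall rate from which to estimate missed events. The enrolment figure of 184 also allows for 15% drop-out, so not every participant would have reached a 12-month call.
- **The 12-month paragraph in section 6.7 is not an exhaustive list.** It omits EQ-5D, which another paragraph and Table 1 place at 12 months, and Figure 1 is not available here. Its silence is therefore weak evidence alone. The empty cell in Table 1 carries the point, and the other paragraph on the telephone contacts agrees with it.

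None of this supplies a 12-month proportion or count of falls and fractures as defined.

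**Conclusion.** The protocol contradicts itself on its safety endpoint. Followed as written, it records falls and fractures for the endpoint up to 3 months, leaves non-serious ones without a scheduled place of record from about day 90 to day 360, and so cannot deliver the 12-month proportion or count. The uncovered window is 270 of 360 days, or 75% (72% to 78% over the visit windows).

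The conclusion rests on two assumptions: that Table 1 is the operative schedule, and that Figure 1 does not add a 12-month falls item. It does not rest on any fall rate. The primary endpoint and the 6-week and 3-month safety results are untouched, and serious events are probably captured. The mismatch should be corrected because a declared safety result is not obtainable and a remedy is inexpensive.

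**What to change.** Choose one of two ways to reconcile the passages.

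1. **Keep 12 months.** Add falls and fractures since last contact (yes/no, and number) to the 12-month call, in both Table 1 and section 6.7. Report the 12-month result with its limits: about nine months of recall, and no data for participants whose 12-month call has already taken place. Give the number of participants who were asked.
2. **End the endpoint at 3 months.** Delete 12 months from the safety endpoint in the synopsis and in section 5.2.

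In either case, state in section 8.2.1 that the exclusion from adverse event reporting does not apply to falls or fractures that meet the SAE definition.

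The first option costs two questions in a call that is already made, a small eCRF change and an amendment. It cannot recover calls already completed. The second costs only an amendment of the text, and it gives up the 12-month safety result.
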